#### 7.2.2 Serious adverse events (SAEs)

A serious adverse event is any untoward medical occurrence or effect that

- results in death;
- is life threatening (at the time of the event);
- requires hospitalisation or prolongation of existing inpatients' hospitalisation;
- results in persistent or significant disability or incapacity;
- is a congenital anomaly or birth defect; or
- any other important medical event that did not result in any of the outcomes listed above due to medical or surgical intervention but could have been based upon appropriate judgement by the investigator.

An elective hospital admission will not be considered as a serious adverse event.

The investigator will report all SAEs to the sponsor without undue delay after obtaining knowledge of the events, except for SAEs that are not considered related to the experimental intervention.

The sponsor will report the SAEs through the web portal *ToetsingOnline* to the accredited METC that approved the protocol:

- within 7 days of first knowledge for SAEs that result in death or are life threatening followed by a period of maximum of 8 days to complete the initial preliminary report.
- within a period of maximum 15 days after the sponsor has first knowledge of the serious adverse events for all SAEs considered related to the experimental intervention.
- in the annual progress report for all SAEs not considered related to the experimental intervention.

#### 7.2.1 Suspected unexpected serious adverse reactions (SUSARs)

Not applicable.

### **7.3 Follow-up of adverse events**

All AEs will be followed until they have abated, or until a stable situation has been reached. Depending on the event, follow up may require additional tests or medical procedures as indicated, and/or referral to the general physician or a medical specialist.

SAEs need to be reported till end of study within the Netherlands, as defined in the protocol.

## 8. STATISTICAL ANALYSIS

### *Data and derived parameters*

The data collected in this study will be both qualitative and quantitative data. An overview is presented in the table below (table 4), showing all the outcome measures, their level of measurement and derived parameters. In the paragraphs below, the statistical analysis of the outcome measures, and how they contribute to answering the study objectives, is described in more detail. An overview of all the (statistical) analyses can be found in table 5.

Table 4. Primary and secondary outcome measures, their characteristics, and derived parameters.

|                            |          |              |                                                                                                                                                                                                                                                                                                                                                                                                                                                                                                                                                                                             |
|----------------------------|----------|--------------|---------------------------------------------------------------------------------------------------------------------------------------------------------------------------------------------------------------------------------------------------------------------------------------------------------------------------------------------------------------------------------------------------------------------------------------------------------------------------------------------------------------------------------------------------------------------------------------------|
| Primary outcome measure    | COPM     | Quantitative | 
 
1. Mean scores of 1-10 range for COPM-P (interval level of measurement).
 
2. Mean scores of 1-10 range for COPM-S (interval level of measurement).
 
                                                                                                                                                                                                                                                                                                                                                                                |
| Secondary outcome measures | ICECAP-A | Quantitative | 
 
1. Descriptive system (5 domains, 4 levels) (ordinal level of measurement).
 
2. Non-weighted sum scores, calculated by summing ICECAP-A item scores (interval level of measurement).
 
3. Total index score obtained by summing preference-based weights (tariff scores) assigned to all different levels, ranging from 0 (no capabilities) to 1 (full capability) (ratio level of measurement).
 
                                                                                                                           |
|                            | USER-P   | Quantitative | 
 
1. Frequency scale; likert scale score 0-5, sum score converted to 0-100 (interval level of measurement).
 
2. Restriction scale; likert scale score 0-3, sum score converted to 0-100 (interval level of measurement).
 
3. Satisfaction scale; likert scale score 0-4, sum score converted to 0-100 (interval level of measurement).
 
                                                                                                                                                                                      |
|                            | SF-36    | Quantitative | 
 
1. Scale scores for the 8 domains, likert scales converted to 0-100 (interval level of measurement) 
 
o physical functioning (PF),
 
o role limitations due to physical health problems (RP),
 
o bodily pain (BP),
 
o general health perceptions (GH),
 
o vitality (VT),
 
o social functioning (SF),
 
o role limitations due to emotional problems (RE),
 
o general mental health (MH).
 
 
 
2. SF-6D scores derived from SF-
 
 |

|       |                                                               |                              |                                                                                                                                                                                                                                          |
|-------|---------------------------------------------------------------|------------------------------|------------------------------------------------------------------------------------------------------------------------------------------------------------------------------------------------------------------------------------------|
|       |                                                               |                              | 36 scores (ratio level of measurement).
3. SF-6D preference-based total index score (ratio level of measurement).                                                                                                                     |
|       | EQ-5D-5L                                                      | Quantitative                 | 1. Descriptive system (5 domains, 5 levels) (ordinal level of measurement).
2. Total index score, ranging from 0 (death) to 1 (full health) (ratio level of measurement).                                                             |
|       | CSWQ                                                          | Quantitative                 | 1. Total score for the capability set (range 0-7; based on the questions calculated whether a capability is present yes/no) (interval level of measurement)
2. Overall question likert scale range 1-5 (ordinal level of measurement) |
| Other | Consultations with health care professionals (audio recorded) | Qualitative and quantitative | Qualitative information
Capability scoring form                                                                                                                                                                                       |
|       | Multidisciplinary team meetings (audio recorded)              | Qualitative and quantitative | Qualitative information
Capability scoring form                                                                                                                                                                                       |
|       | Medical reports                                               | Qualitative and quantitative | Qualitative information
Capability scoring form                                                                                                                                                                                       |
|       | Questionnaire on resources and personal characteristics       | Quantitative and qualitative | Descriptive data (nominal and ordinal)                                                                                                                                                                                                   |
|       | Interview on experiences with provided care (audio recorded)  | Qualitative                  | Qualitative information                                                                                                                                                                                                                  |
|       | Focus groups with health care professionals (audio recorded)  | Qualitative                  | Qualitative information                                                                                                                                                                                                                  |

Table 5. Overview of the (statistical ) analyses per research objective.

| Objective                                                                                              | Outcome measures                        | Analysis                                                                                                                                                   | Statistical test |
|--------------------------------------------------------------------------------------------------------|-----------------------------------------|------------------------------------------------------------------------------------------------------------------------------------------------------------|------------------|
| To compare the quality of life of patients with NMD receiving capability care versus usual care | COPM usual care
COPM capability care | COPM-P usual care T1 vs. COPM-P capability care T1 (T0 scores as covariate)
COPM-S usual care T1 vs. COPM-S capability care T1 (T0 scores as covariate) | ANCOVA           |

|                                                                                                                                                                                                                                              |                                                                                                                                                                                                                          |                                                                                               |                         |
|----------------------------------------------------------------------------------------------------------------------------------------------------------------------------------------------------------------------------------------------|--------------------------------------------------------------------------------------------------------------------------------------------------------------------------------------------------------------------------|-----------------------------------------------------------------------------------------------|-------------------------|
| To develop rehabilitation care for patients with NMD that is based on the capability approach                                                                                                                                         | Consultations with health care professionals
Multidisciplinary team meetings
Medical reports
Interview on experiences with provided care                                                                        | Qualitative analysis                                                                          | N/A                     |
| To assess treatment fidelity in designing capability care, training of the health care professionals in providing capability care, delivery of capability care, and receipt and enactment of capability care by the patients with NMD | Consultations with health care professionals
Multidisciplinary team meetings
Medical reports
Interview on experiences with provided care
Focus groups with health care professionals                         | Qualitative analysis
Capability scoring form (to be developed)                             | N/A
To be determined |
| To determine how capability care, in comparison to usual care, facilitates changes in resources and conversion factors, enlarging functionings and capabilities                                                                       | Consultations with health care professionals
Medical reports
Questionnaire on resources and personal characteristics
Interview on experiences with provided care
Focus groups with health care professionals | Qualitative analysis                                                                          | N/A                     |
| To compare the capabilities outcome of patients with NMD receiving capability care versus usual care, using the ICECAP-A that                                                                                                         | ICECAP-A usual care
ICECAP-A capability care                                                                                                                                                                          | Non-weighted ICECAP-A sum scores usual care T1 vs capability care T1 (T0 scores as covariate) | ANCOVA                  |

|                                                                                                                                                                                                                                    |                                                                                                                                                         |                                                                                                                                                                    |                                   |
|------------------------------------------------------------------------------------------------------------------------------------------------------------------------------------------------------------------------------------|---------------------------------------------------------------------------------------------------------------------------------------------------------|--------------------------------------------------------------------------------------------------------------------------------------------------------------------|-----------------------------------|
| covers five attributes (e.g. attachment, stability, achievement, enjoyment, autonomy) of wellbeing                                                                                                                          |                                                                                                                                                         |                                                                                                                                                                    |                                   |
| To compare the participation outcome (USER-P) of patients with NMD receiving capability care versus usual care                                                                                                              | USER-P usual care
USER-P capability care                                                                                                             | USER-P usual care T1 vs. USER-P capability care T1 (T0 scores as covariate)                                                                                        | ANCOVA                            |
| To compare the work capabilities outcome (CSWQ) of patients with NMD receiving capability care versus usual care                                                                                                            | CSWQ usual care
CSWQ capability care                                                                                                                 | CSWQ total score usual care T1 vs. CSWQ total score capability care T1 (T0 scores as covariate)

CSWQ overall question (T1-T0) usual care vs capability care | ANCOVA

Mann Whitney U test |
| To determine whether the use of a broader measure of quality of life (ICECAP-A), compared to a health-related quality of life measure (EQ-5D-5L, SF-36), leads to other outcomes in terms of assessing the benefits of care | ICECAP-A usual care
ICECAP-A capability care

EQ-5D-5L usual care
EQ-5D-5L capability care

SF-36 usual care
SF-36 capability care | Multiple comparisons between usual care group and capability care group on difference T1-T0.                                                                       | ANCOVA, contingency table         |

### *Handling of missing data*

The data collected from subjects that have withdrawn from the study will not be used, as this will only consist of baseline measurements when a subject has withdrawn. With the present study design, consisting of only two measurement moments, it is not possible to use an intention-to-treat analysis for the subjects that have withdrawn. However, the number of withdrawals and reason for withdrawal (if the patient is prepared to share his reason) will be described. With the collected baseline-data and reasons for withdrawal, we will analyse whether there is a certain pattern to be found for patients withdrawing from the study.

Missing data from incomplete measures will be excluded from the analyses. However, this subject will not be completely excluded from all analyses. For example, when the subject has completed all measurement moments for the primary outcome measure but not for one of the secondary outcome measures, we will include the data for the primary outcome measure in the analysis, but exclude the data for the incomplete secondary outcome measure. Or, if the primary outcome measure is missing but the secondary outcome measures are complete, we

will exclude the data for the primary outcome measure, but include the data for the secondary outcome measures.

## 8.1 Primary study parameters

### *Primary outcome measure*

The primary outcome measure is the COPM. The COPM performance (COPM-P) and satisfaction (COPM-S) scales provide continuous data.

For the COPM, the performance score (COPM-P) and satisfaction score (COPM-S) are derived from the scores on the individual problems in activities, divided by the number of activities:

$$\text{COPM performance score (COPM-P)} = \frac{\text{sum score performance}}{\text{number of activities}}$$

$$\text{COPM satisfaction score (COPM-S)} = \frac{\text{sum score satisfaction}}{\text{number of activities}}$$

### *Statistical analysis*

Data will be visualised using scatter-plots, box plots and histograms. Descriptive statistics will include mean and standard deviation. To answer the primary research question, whether there is a difference in improvement at T1 between the capability care and usual care group, an ANCOVA model will be fitted. Covariates will be the T0 scores of both groups, age, gender and diagnosis. With the model it is tested whether an intervention-effect is present. For an intervention-effect to be present, the scores on both the COPM-P and COPM-S will need to show a significant change. A p-value below 0.05 will be considered significant.

## 8.2 Secondary study parameters

For the following secondary study parameters, similar analyses as described above (ANCOVA model) will be performed:

- ICECAP-A preference-weighted index score
- ICECAP-A non-weighted sum score
- USER-P
- CSWQ total score
- EQ-5D-5L preference-weighted index score
- EQ-5D-5L non-weighted sum score
- SF-36 preference-weighted index score
- SF-36 non-weighted sum score

The CSWQ overall question will be analysed using a Mann-Whitney U test. Median and range will be described. The Mann Whitney U test will be performed on the difference score between T1 and T0, to determine whether there is a difference between the usual care and capability care group. A p-value below 0.05 will be considered significant.

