#### 4.4 Sample size calculation

In this study the primary outcome measure is the COPM, which consists of the performance score (COPM-P) and satisfaction score (COPM-S). Both COPM-P and COPM-S scores at 6 months after baseline (T1), corrected for the value at baseline (T0), will be used. Both outcomes are considered equally important and the researchers consider the proposed treatment as successful only if for both outcomes the capability care group performs significantly better than the group that is given treatment as usual.

For COPM-P a difference of 1.4 is expected between the usual care group and the capability care group at time T1 (when scored blinded). For COPM-S this expected value is 1.9. These values represent a clinically relevant improvement as perceived by the client (Eyssen et al., 2011). The standard deviations in both groups and for both outcomes are expected to be 1.9 at time T1 (Veenhuizen et al., 2019).

Treatment is considered to be successful only if for both outcomes a difference can be shown. That means that a sample size calculation has to be done for the two outcomes combined in which the correlation between the outcomes should be taken into account. This correlation will be positive in this study; it is expected to be close to 1. The most conservative sample size (highest sample size) will be obtained if we require a type I error of at most the significance level for either test (corresponds to a correlation close to one) and the multiplication of the powers of the two tests is equal to the desired power of the total test (corresponds with independent test-statistics). For this situation, and under the assumptions given in the previous paragraph, a sample size of at least 24 patients per group will yield a power of 80% to show a statistical difference between the treatment and the usual-care groups at significance level 0.05. These calculations are based on ANCOVA-models with the outcome at 6 months as dependent variables, corrected for the value at baseline and an assumed correlation of 0.5 between the outcome values at T0 and the T1 (Borm, Fransen, & Lemmens, 2007).

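### The CSWQ overall question is tested on unadjusted T1-T0 differences of an ordinal item, while the other scores listed in section 8.2 get a baseline-adjusted model

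*Protocol*

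**What the plan says.** Table 4 (Protocol section 8) lists the second CSWQ parameter as "Overall question likert scale range 1-5 (ordinal level of measurement". Section 8.2 assigns it a Mann-Whitney U test and specifies: "The Mann Whitney U test will be performed on the difference score between T1 and T0". Table 5 gives the same comparison, "CSWQ overall question (T1-T0) usual care vs capability care", with no covariate. The significance rule is "A p-value below 0.05 will be considered significant".

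The eight scores listed at the start of section 8.2, including the CSWQ total score, are to be analysed like the primary outcome. For that model section 8.1 states: "Covariates will be the T0 scores of both groups, age, gender and diagnosis".

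Two other places matter. Section 6.2 describes two cohorts treated at different times, without randomisation. Section 6.1.2 restricts the CSWQ to employed patients, including the self-employed, and does not say how many are expected.

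**The concern.** The plan treats the item in two incompatible ways. Calling it ordinal means that the distance from 1 to 2 need not equal the distance from 4 to 5. Subtracting T0 from T1 assumes that it does, and ranking the differences afterwards does not undo that.

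The scale is also bounded. A patient who answers 5 at T0 can only stay or fall, and one who answers 1 can only stay or rise. The difference therefore carries the T0 level with it. If one cohort starts higher, the comparison of differences is tilted before any treatment effect enters.

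The plan adjusts its neighbouring scores for T0, age, gender and diagnosis, which is sensible for sequential cohorts, and drops all four here without giving a reason. At stake are the precision and the robustness to baseline imbalance of one part of the work-capability objective, in a subgroup that is already small.

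**Working it through.** **1. The plan's own power figure.** Section 4.4 covers the COPM only: "For COPM-P a difference of 1.4 is expected between the usual care group and the capability care group at time T1" and "For COPM-S this expected value is 1.9", with SD 1.9 and a T0-T1 correlation of 0.5. The residual SD is 1.9 × √(1 − 0.5²) = 1.645. With a noncentral t (2n − 3 degrees of freedom, two-sided 0.05), power for COPM-P is 0.805 at n = 23. The product of the COPM-P and COPM-S powers is 0.801 at n = 24. Both stated sample sizes are reproduced. Nothing equivalent exists for the CSWQ overall question, so COPM values can only be borrowed as assumptions. The COPM-P effect is 1.4/1.9 = 0.74 SD.

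**2. Dependence of the change score on T0.** Even for an unbounded score with equal variances, Corr(T1 − T0, T0) = −√((1 − ρ)/2):
- ρ = 0.3: −0.59
- ρ = 0.5: −0.50
- ρ = 0.7: −0.39

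The bounds of a five-level item add to this.

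**3. Closed form for a continuous analogue.** The error variance is proportional to 2(1 − ρ) for a change score and to 1 − ρ² for ANCOVA, so the relative efficiency is (1 + ρ)/2. Multiplying by 0.955 for Mann-Whitney at ρ = 0.5 gives 0.75 × 0.955 = 0.716. If ANCOVA has 80% power, the planned approach has Φ((1.96 + 0.842) × √0.716 − 1.96) = Φ(0.41) = 0.66, a loss of 14 points. The losses at ρ = 0.3, 0.7 and 0.8 are 20, 9 and 6 points. The factor 0.955 is the price of ranking. A rank analysis of covariance pays something similar, so not all of this loss can be recovered.

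**4. Simulation of the item.** Bivariate normal latent scores were cut into five levels, with mid-scale and near-ceiling versions, 15 to 20 per group and correlation 0.3 to 0.7. All of these settings are assumptions. The planned test was compared with a rank analysis of covariance on T0.

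| Assumed shift | Gain in power from T0 adjustment |
|---|---|
| 0.3 SD | about 2-5 points |
| 0.5 SD | 5-12 points |
| 0.74 SD | 9-24 points |

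Type I error of the rank analysis of covariance was 4-6%. With all four covariates it stayed in that range, and the gain was somewhat smaller when the three added covariates were unrelated to the response.

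**5. Sensitivity to T0 imbalance.** With no treatment effect, both tests have an overall type I error of about 4-6%. Among samples whose T0 means differ by at least 0.5 level, the planned test rejects in 7-15%, against 2-7% for the rank analysis of covariance.

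**6. Proportional-odds comparator.** Against a T0-adjusted proportional-odds model, over correlations of 0.3 to 0.8, shifts of 0.3 to 1.0 SD and 10 to 30 per group, the planned test loses about 3 to 34 points. After correction for the size of the comparator this becomes about −2 to 27 (correlations 0.5 to 0.8). The correction matters because the T0-adjusted model itself ran at 5-10% under the null. With age, gender and diagnosis added, its type I error was 7-13% (likelihood ratio) or 5.5-9.5% (Wald) at 10 to 20 per group. For a near-ceiling item at least one response level was empty in 43-70% of samples.

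**The case against.** The strongest defence is that the planned test is valid in the ordinary sense. It uses T0 through the difference, and it holds its overall type I error when the cohorts come from the same population. In non-randomised cohorts a change-score comparison and a T0-adjusted comparison answer different questions, and neither removes baseline imbalance by design. The item is one question in one secondary instrument, and the CSWQ total score already serves the same objective with ANCOVA. All of this stands, and it is why the point is minor. It does not explain why the plan adjusts the CSWQ total score but not the overall question from the same patients. Ordinal data can be analysed with covariates.

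Three stronger readings are tempting, and the documents do not support them.
- A reader might infer a fixed loss of 15 to 25 points. The protocol supplies none of the inputs, and the loss is small for small effects.
- A reader might infer that this is the only unadjusted comparison in the plan. Section 8.2 also plans responder contingency tables and an anchor-based comparison of mean ICECAP-A changes, and section 8.3.2 leaves the method for the capability scoring form open.
- A reader might conclude that a proportional-odds model with all covariates is the obvious replacement. At these sample sizes it can be liberal and often meets empty categories.

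**Conclusion.** The point holds as a minor one. The protocol fixes this test explicitly, so the choice has not been left to a later analysis plan. It conflicts with the ordinal label in Table 4 and omits the covariates used for the other scores listed in section 8.2. The direction of the power loss is clear under the simulated conditions. Its size depends on assumed values for the number employed, correlation, T0 distribution and effect, and the upper end of the range requires an effect as large as the one planned for COPM-P. Protection against T0 imbalance matters at least as much as power, because the cohorts are sequential. The trial's success rule, which rests on COPM-P and COPM-S, is unaffected.

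**What to change.** In section 8.2 and Table 5, replace the Mann-Whitney test on T1-T0 with a rank analysis of covariance: the ranked T1 response regressed on group, with ranked T0 response, age, gender and diagnosis as covariates. Keep the median and range as description. A proportional-odds model with an odds ratio and 95% CI may be added as supportive if no response category is empty, with a note that it can be liberal at 10 to 20 per group.

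The cost is one sentence in section 8.2 and one cell in Table 5, with no new data. The drawbacks are a less direct effect estimate from the rank model and a few degrees of freedom spent on covariates in a small subgroup.
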